**Methods:**

In this prospective study, 304 youths aged 15 to 24 years (n=152, 50% who smoke only e-cigarettes and n=152, 50% who do not smoke e-cigarettes or cigarettes) will be divided into 2 groups for a controlled study. Whether e-cigarettes cause oral mucosal lesions will be verified by comparing the odds of oral mucosal lesions in the 2 experimental groups. For this experiment, the predefined power is 80% (*P*=.04), and the predefined proportions of groups 1 and 2 are 11% and 2.5%, respectively.

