### Hypothesis

This study hypothesizes that e-cigarettes, in the speculated absence of tobacco, may still induce carcinogenesis. Alternatively, it is suggested that this habit may trigger an imbalance in the oral microbiome that predisposes the mucosal epithelium to oral cavity cancer with other etiological factors. This presupposed risk is likely proportional to the frequency and duration of e-cigarette smoking. The oral mucosal health of participants will be determined by determining the presence of white spots in the mouth (the main feature of the oral mucosa that is damaged by smoking behavior).

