### Data Analysis

Descriptive statistics will be used for all binary, categorical, and continuous variables and expressed as tables, texts, and figures. Bivariate analysis will then be performed for relevant variables. The Shapiro-Wilks test will be performed for continuous variables to determine whether they follow the Gaussian distribution. Afterward, the independent 1-tailed *t* test and 1-way ANOVA will be used; otherwise, the Mann-Whitney *U* test and Kruskal-Wallis test will be performed. For cross-tabulation of 2 categorical variables, the chi-square test will be used. Variables that do not fulfill the assumption of this test will be analyzed using Fisher exact test. Comparisons with *P*=20 will be used to implement multivariable analysis using multiple logistic regression. Odds ratios and 95% CIs will be determined for e-cigarette smoking and other individual factors. For all analyses, *P*<.05 will be used to denote statistical significance. Statistical analyses will be performed using the SPSS (version 27; IBM Corp).

The control and e-cigarette groups will be subjected to a *t* test (assuming the data meet the normality criteria and do not meet the criteria for the rank sum test) to verify whether e-cigarettes cause harm.

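### The sentence on verifying harm names a normality-conditional t test, but the outcome is yes/no white spots, which can never meet that condition and is elsewhere to be judged by odds

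*Protocol article*

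**What the plan says.** Protocol article only; no separate analysis plan is shown.

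- **Outcome.** The Hypothesis section assesses mucosal health by "determining the presence of white spots in the mouth". The questionnaire records the same item as present or not.
- **Sizing.** Sampling Methods plans 152 per group on proportions of 11% and 2.5%, with 80% power and P=.04. The number of sides is not given.
- **Deciding comparison, Abstract.** Whether e-cigarettes cause lesions is to be verified by "comparing the odds of oral mucosal lesions in the 2 experimental groups".
- **Deciding comparison, Data Analysis.** The closing sentence gives that job to a t test between the two groups, "assuming the data meet the normality criteria and do not meet the criteria for the rank sum test) to verify whether e-cigarettes cause harm". It names neither the variable nor the number of tails.
- **General rules, Data Analysis.** After a Shapiro-Wilk check of continuous variables, the "independent 1-tailed *t* test and 1-way ANOVA will be used"; "otherwise, the Mann-Whitney *U* test and Kruskal-Wallis test will be performed". Then: "For cross-tabulation of 2 categorical variables, the chi-square test will be used", with Fisher's exact test as fallback. Selected comparisons "will be used to implement multivariable analysis using multiple logistic regression", reported as odds ratios with 95% CIs. The significance threshold is P<.05 throughout.

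**The concern.** Two places in the article say how the main question will be answered, and they name different comparisons: odds in the Abstract, a t test in Data Analysis. The second does not suit the outcome, because its own condition fails for any yes/no variable. Followed literally, it sends the main comparison to a rank-sum test whose tails are not stated and which estimates no odds ratio. The same section offers chi-square or Fisher and logistic regression for the same data, and ranks none of them as primary.

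At stake is a main inference left to be settled after the data are seen. The tests mostly agree when the effect is large, but they can fall on opposite sides of .05 when it is moderate, especially if the number of tails is also open. Research Significance says a positive result would be used to warn users and guide legislation, so this should be fixed in advance.

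**Working it through.** **Inputs.** 152 per group, 11% versus 2.5%, 80% power and P=.04 (Sampling Methods); P<.05 and the list of tests (Data Analysis). Expected events: 0.11 × 152 = 16.7, taken as 17, and 0.025 × 152 = 3.8, taken as 4; about 21 in all.

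**1. The plan's own sample size.** Pooled formula, n per group = [z_α √(2p̄(1−p̄)) + z_0.80 √(p1(1−p1) + p2(1−p2))]² / (p1−p2)², with p̄ = 0.0675 and p1−p2 = 0.085:

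| α | Sides | n per group | With continuity correction | Power at 152 (pooled, uncorrected) |
|---|---|---|---|---|
| .04 | 2 | 145 | 168 | 81.9% |
| .05 | 2 | 136 | 159 | 84.3% |
| .04 | 1 | 116 | 139 | 88.9% |
| .05 | 1 | 107 | 130 | 90.8% |

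No row gives exactly 152, and the sizing appendix is not shown. The figure lies among the two-sided values and above every one-sided value, so it sits better with a two-sided comparison of proportions. An unstated allowance for losses could also explain a gap, so this is an indication only.

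**2. Can the normality condition be met?** Shapiro-Wilk on 0/1 data:

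- 17 of 152: W = 0.36, P = 6e-23.
- 4 of 152: W = 0.15, P = 7e-26.
- 76 of 152, the most balanced split: W = 0.64, P = 8e-18.

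It cannot be met at this sample size.

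**3. Does the choice of statistic matter at the planned effect?** For 17/152 versus 4/152, two-sided P is .0032 (t), .0033 (rank-sum) and .0033 (chi-square). The t statistic itself distorts little. What changes the error rate is the single tail.

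**4. If the one-tailed t test were applied to lesions at .05.** Exact enumeration over Binomial(152, p) in both groups gives the chance of declaring harm when the true rates are equal:

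| Common rate | One-tailed t | Two-sided t or chi-square | Two-sided Fisher |
|---|---|---|---|
| 2.5% | 6.1% | 2.2% | 0.8% |
| 5% | 4.9% | 2.4% | 1.2% |
| 6.75% | 5.1% | 2.4% | 1.4% |
| 11% | 5.0% | 2.5% | 1.7% |

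Total type I error, both directions together, is 4.4-5.0% for the two-sided chi-square test. For the one-tailed test it is the column shown.

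**5. A table where the choice decides.** Take 11/152 versus 4/152. The difference is 0.04605 and the pooled variance is [11(1−11/152) + 4(1−4/152)]/302 = 0.04668. Then t = 0.04605/√(0.04668 × 2/152) = 1.858. One-tailed P = .032; two-tailed P = .064. The chi-square test, with p̄ = 15/304 = 0.04934, has z = 0.04605/√(0.04934 × 0.95066 × 2/152) = 1.854, P = .064. Rank-sum P = .064 and Fisher P = .109. With 4 control events, two-sided significance at .05 needs 12 events in the e-cigarette group by chi-square and 13 by Fisher.

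**6. Power at 11% versus 2.5%, 152 per group, α = .05, exact.** One-tailed t 93.0%; two-sided chi-square 87.0%; two-sided Fisher 81.5%. With Fisher at .04, power is 78.9%.

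**The case against.** A reader might infer that harm will be decided by an unadjusted one-tailed t test that doubles the false-positive rate. The documents do not support that reading, for four reasons.

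- If normality always fails, the plan's own rule never runs the t test on this outcome. It moves to the rank-sum test, whose tails are not stated. On that path no doubling is shown.
- The closing sentence gives no number of tails. The only statement is in the rule for continuous variables: "Afterward, the independent 1-tailed". The sample size also sits better with two sides.
- The increase is in the harm direction only, and follows by definition from putting the whole .05 in one tail.
- Calling this test the deciding one, and unadjusted, is contested by the article itself. The Abstract compares odds, and Data Analysis already plans chi-square or Fisher and then multivariable logistic regression with odds ratios for e-cigarette smoking.

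There is also a residual doubt about the variable: the questionnaire section says answers will be converted to objective scores. No lesion score is defined, however, and the Hypothesis, the questionnaire item and the sizing all treat the outcome as present or absent.

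All of this limits the error-rate claim to a conditional one. It does not remove the inconsistency. The sentence on verifying harm still names a test whose condition cannot hold, and suitable analyses elsewhere in the section are not given precedence over it.

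**Conclusion.** The point holds as an inconsistency in the main analysis. The t-test sentence is wrong for a binary outcome, conflicts with the odds comparison in the Abstract, and conflicts with the categorical and logistic analyses in its own section. That normality cannot be met is certain if the analysed variable is presence of white spots, which is the only lesion outcome the article defines.

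The error-rate consequence is conditional. It arises only if the one-tailed t test is applied to lesions despite the failed condition. The chance of falsely declaring harm would then be about 5-6% instead of 2.2-2.5%, and a table such as 11/152 versus 4/152 would move from P=.064 (two-sided chi-square) to P=.032. The figures assume 152 analysed per group and equal true rates between 2.5% and 11%. With the planned rates the tests agree, so the practical risk lies in moderate effects.

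**What to change.** In Data Analysis:

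1. Delete the closing t-test sentence for the lesion outcome.
2. Name one primary analysis, for example: presence of white spots is compared between groups by logistic regression, two-sided at .05, reporting the odds ratio with 95% CI and adjusting for a short list of covariates fixed in advance.
3. Keep that list very small: only about 21 events are expected.
4. Present the unadjusted chi-square test, or Fisher's exact test where its assumptions fail, as supportive.
5. Keep t and Mann-Whitney tests, two-sided, for continuous variables only.
6. State the sides of the sample-size test, and reconcile its P=.04 with the .05 used for analysis.

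**Cost.** Rewording of one section before any data are collected, and a slightly stricter threshold for declaring harm. At .05 no extra participants are needed for the unadjusted two-sided tests, as the power figures above show. Fisher falls just short of 80% if .04 is the intended level. None of these figures is the power of the adjusted logistic model, which should not be claimed until it has been calculated.

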## Results

This experiment is at the conceptualization phase and has not yet been carried out. Experimenters have not been recruited and no data have been collected.

## Discussion

In examining the potential negative impact of e-cigarettes on the oral mucosa, this study deliberately focused its investigation on this specific aspect, excluding other potential confounding factors that might influence the results. Notably, variables such as alcohol consumption, daily routines, and gender differences were not considered in the experimental design. While these factors were omitted from this study, they were duly documented in the questionnaire phase, laying the groundwork for future investigations to delve into these variables. This strategic choice aimed to isolate the primary relationship between e-cigarette use and oral mucosal health, with the intention to refine and expand the scope in subsequent research endeavors.

The findings of this study align with existing literature on e-cigarettes, which suggests a correlation between the chemicals present in e-cigarettes and cytotoxicity, leading to damage to the oral mucosa. This corroborates with prior research, providing further evidence of the potential harm associated with e-cigarette use [10,16,17]. The recognition of this association holds significant implications for public health, emphasizing the need for awareness campaigns and regulatory measures to mitigate the adverse effects on oral health. Moreover, the study acknowledges the diverse landscape of e-cigarettes in the United States, encompassing various brands and flavors, each containing distinct chemical compositions. Given this complexity, it is acknowledged that the study does not comprehensively analyze all individual chemicals present in different e-cigarettes. This limitation prompts a call for future experiments to undertake a more nuanced examination of the diverse chemical profiles within e-cigarettes to better understand their distinct impacts on oral mucosal tissues.

Despite the valuable insights provided by this study, certain limitations should be acknowledged. The decision to exclude factors such as alcohol consumption and daily routines may have implications for the generalizability of the findings. In addition, the complexity of e-cigarette compositions poses a challenge, as the study did not extensively investigate the myriad chemicals present in different e-cigarette products. Future research endeavors should consider a more comprehensive approach, encompassing a broader range of variables and a detailed analysis of the chemical constituents of various e-cigarettes.

In conclusion, this study contributes valuable evidence to the growing body of knowledge on the potential negative impact of e-cigarettes on oral mucosal health. By focusing on a specific aspect while recognizing its limitations, this research paves the way for future investigations to build upon these findings. The implications extend beyond the immediate scope of oral health, emphasizing the broader need for public health interventions and regulatory measures in response to the evolving landscape of e-cigarette use.

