## Introduction

### Background

Oral cavity cancer is the most prevalent head and neck malignancy worldwide [1,2]. This malignant phenotype is often associated with habitual and lifestyle factors, such as tobacco smoking, excessive alcohol consumption, betel nut chewing, and low intake of fruits and vegetables [1]. Due to restrictive government policies and proven negative health effects in many parts of the world, the use of tobacco has declined in recent decades [3]. Electronic cigarettes (e-cigarettes) were invented by a Chinese pharmacist, Hon Lik, in 2003, who envisioned that they would replace conventional cigarettes due to their deleterious effects [4]. e-Cigarette companies claim that handheld devices can provide smokers with the same experience as conventional cigarettes while reducing their negative effects. e-Cigarettes were introduced with the hope that the smoking population would gradually stop using conventional cigarettes and switch to e-cigarettes. With the waning consumption of regular cigarettes, the use of e-cigarettes has surged worldwide, indicating that smokers now consider e-cigarettes viable replacements. Moreover, recent data have indicated that e-cigarette smoking practices are more common among teenagers and young adults [5,6]. However, most people do not take this soaring statistic seriously and allow young people to use e-cigarettes freely. Most people believe that the health hazards of smoking only manifest with increasing age and, thus, concern is unnecessary regarding the use of e-cigarettes by young people.

It is no surprise that young adults are the primary habitual e-cigarette users. The portability of the devices, different flavors with less nicotine, and convenient use of e-cigarettes make them appealing to young people. Data from the 2011-2018 National Youth Tobacco Survey in the United States demonstrated that e-cigarette use among high school students increased from 1.5% in 2011 to 20.8% in 2018 [3]. In 2022, the Centers for Disease Control and Prevention indicated that 2.55 million US middle and high school students reported current (past 30 days) e-cigarette use; nearly 85% of these young people used flavored e-cigarettes, and more than half used disposable e-cigarettes [7]. This increase has also become noticeable in community settings. Unfortunately, adults do not pay enough attention to the use of e-cigarettes, especially in schools.

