### Data Collection: Questionnaire

Interviewer-administered questionnaires will be used to collect data on demographic, lifestyle, and socioeconomic variables for the cases and controls. The questionnaire tool will comprise 2 parts: exposure information (part A) and sociodemographic information (part B). A life grid sheet will be used during interviews to efficiently collect retrospective information on lifestyle habits and other risk factors. To reduce observer bias, interviewers will not initially be informed about the aim of the research. Once cases are identified and interviewed, matching controls will be recruited and interviewed. Answers provided by participants will be converted to objective scores after data collection by the investigator (SC). The details on the parts of the questionnaire are as follows.

Exposure information (part A) will include (1) oral mucosal health status (whether white spots are present), (2) smoking habits, (3) type of products used, (4) e-cigarette smoking status (yes or no and current or previous), (5) age of onset, (6) duration of smoking, (7) pattern of smoking duration (continuous or intermittent), (8) frequency of smoking (daily, weekly, and occasionally), (9) number of cartridges (frequency), and (10) Tobacco consumption. Sociodemographic information (part B) will include (1) age, (2) sex, (3) occupation type, (4) education level, (5) income, and (6) ethnicity.

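### The Discussion says alcohol and daily routines are recorded in the questionnaire, but the itemised questionnaire names neither, and for alcohol the gap falls on the e-cigarette group

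*Protocol article*

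**What the plan says.** The Discussion explains that the study concentrates on e-cigarettes and the oral mucosa and sets other possible confounders aside: "variables such as alcohol consumption, daily routines, and gender differences were not considered in the experimental design". It then gives the reassurance that matters here, with later research in view: "While these factors were omitted from this study, they were duly documented in the questionnaire phase".

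The Methods section Data Collection: Questionnaire describes a form in two parts. Part A begins: "Exposure information (part A) will include (1) oral mucosal health status (whether white spots are present), (2) smoking habits, (3) type of products used". It goes on through e-cigarette status, age of onset, duration, pattern and frequency of smoking, and closes with "9) number of cartridges (frequency), and (10) Tobacco consumption". Part B holds "1) age, (2) sex, (3) occupation type, (4) education level, (5) income, and (6) ethnicity". The same section says in general terms that lifestyle variables will be collected, and that a life grid sheet will be used at interview for past habits and risk exposures. It does not say which ones.

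Two other places bear on the point. Background lists lifestyle factors often associated with oral cavity cancer, "such as tobacco smoking, excessive alcohol consumption, betel nut chewing, and low intake of fruits and vegetables". Selection of Controls admits only people with no history of drinking alcohol, whereas the inclusion and exclusion criteria for the e-cigarette group do not mention alcohol.

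**The concern.** The article makes a positive statement about what its instrument contains, and its own itemised list does not bear that out. This is more than detail left to a fuller document: the list goes down to the number of cartridges, and the Discussion then describes it as holding something that it does not show.

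For daily routines the consequence is mainly for the later research that the Discussion has in mind. For alcohol it also reaches this study. Drinking is excluded in one group and unrestricted in the other, the article itself counts excessive drinking among the factors linked to oral cavity cancer, and the outcome, white spots, is used as a marker of mucosal damage. If e-cigarette users drink and controls by definition do not, part of any difference in white spots could be due to alcohol. An alcohol field in the e-cigarette group is the least that is needed to examine this.

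**Working it through.** No figure in the plan has to be reproduced. The check sets the listed items against the factors that the Discussion says are recorded.

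**Step 1. Count the items.** Part A has 10 and Part B has 6, so 10 + 6 = 16 listed fields.

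**Step 2. Match them to the three factors named in the Discussion.**

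| Factor | Listed fields that cover it | Where |
|---|---|---|
| Gender | 1 | Part B, item 2 (sex) |
| Alcohol consumption | 0 | none |
| Daily routines | 0 | none |

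The only use of the word daily in the list is as a category of smoking frequency. So 2 of the 3 factors have no listed field.

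**Step 3. Look for another place where they could be collected.** The general reference to lifestyle variables and the life grid sheet are the only candidates. Either could hold alcohol or routines; neither names them.

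**Step 4. Find who is affected.** The planned sample is 152 + 152 = 304.

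- Alcohol: eligibility fixes the drinking history of the 152 controls as none. The gap therefore concerns the 152 e-cigarette users, 152/304 = 50% of the sample.
- Daily routines: no eligibility criterion touches them, so the gap concerns all 304.

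**Step 5. Follow alcohol into the analysis.** Data Analysis plans bivariate comparisons and then multiple logistic regression, with odds ratios for e-cigarette smoking and other individual factors. A variable that was not recorded can be neither screened nor entered. With drinking coded yes or no, eligibility leaves three possible cells:

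1. controls who do not drink;
2. e-cigarette users who do not drink;
3. e-cigarette users who drink.

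A logistic model with an intercept, an e-cigarette term and a drinking term has three parameters for these three cells. Without other covariates, its e-cigarette odds ratio is therefore exactly the comparison of cell 2 with cell 1. Adjustment and restriction to non-drinkers then give the same answer, and both need to know which users belong in cell 2. Without an alcohol field, cells 2 and 3 cannot be told apart, and only the mixed comparison of (2 + 3) with 1 is available.

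**The case against.** The strongest reply is that the list need not be the whole instrument. The article condenses a longer plan, says only what each part will include, mentions lifestyle variables as a class, and describes a life grid in which alcohol would be a natural entry. An expert panel is still to assess the form's face and content validity. This stands as far as it goes: a field that is not specified is not proved absent. It does not remove the contradiction, because the Discussion says these particular factors are recorded and no part of the described instrument names them. If the life grid is meant to hold them, saying so would be a sufficient repair.

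Several stronger readings are tempting and are not supported:

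- A reader might infer that the data will not exist. The life grid leaves their collection possible.
- A reader might infer that the plan relies on these data. The Discussion sets the factors aside for future work and admits their exclusion as a limitation, and Data Analysis names neither.
- A reader might infer that alcohol data are missing for all 304 participants. The control criterion settles drinking history for 152 of them.
- A reader might infer that the omission could not be repaired after a single interview. The article nowhere says that there is only one, and Study Design describes following participants over time.
- A reader might add betel nut and diet, which Background lists and the form also lacks. The Discussion never says that they are recorded, so their absence contradicts nothing.

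One could also say that the unequal alcohol criterion is an eligibility matter. It is, but it is also why an alcohol field in the e-cigarette group matters.

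**Conclusion.** The point holds as a contradiction between the Discussion and the itemised questionnaire: 2 of the 3 factors said to be recorded, alcohol and daily routines, have no field among 16 and are not named in the life grid. For alcohol the gap concerns the 152 e-cigarette users; for daily routines, all 304 participants.

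The alcohol gap carries the weight. Controls are non-drinkers by selection and users are not, so a possible confounder can be unbalanced by design in the very group where it is not specified to be measured. How much bias could follow cannot be computed from the article, which gives neither the frequency of drinking among e-cigarette users nor its effect on white spots.

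The conclusion assumes that the form is fielded as listed, that the life grid adds no alcohol or routine entry, and that the control criterion means no drinking history at all. If that criterion were read as not drinking at recruitment, past drinking among controls would be unspecified too. This should be put right before fielding; it does not by itself invalidate the study.

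**What to change.** - Add to Part A an alcohol item (ever or current use, and amount) and a daily-routine item that defines what is meant, since the article leaves the term open. Naming both explicitly as life grid entries would serve equally well. Use the same wording in both groups.
- State in Data Analysis that alcohol is a candidate for the logistic regression, or that non-drinking e-cigarette users will be compared with the non-drinking controls.
- Make the Discussion agree with the final instrument.

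Correcting the Discussion sentence alone would remove the contradiction but leave alcohol unspecified in the e-cigarette group. Items on betel nut and diet are optional and not part of this point.

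The cost is a few short questions and two or three edited sentences. The timing is good: Results states that no data have been collected, and the expert panel has yet to assess the form, so the items can go through that step with the rest.
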